### **6.1 Efficacy Analysis**

Efficacy will be estimated by providing the incidence of lesion failure by 6-months. Assuming we will enroll patients providing 2 lesions on average, we expect to acquire 70 lesions for the entire cohort of 35 treated patients. The information below provides the estimated boundaries of exact 95% CIs for varying sample sizes. As futility monitoring is employed at the patient-level, there is potential to terminate the trial early. We presuppose 40 lesions if the trial is stopped after the first stage, and 70 lesions if the trial runs through both stages. Details regarding the futility assessment are described below.

The sample size justification for our primary endpoint is based on the incidence of lesion failure. By assuming a 6-month incidence rate of 0.50, the bounds of the 95% exact CI will not extend beyond these limits: (0.34, 0.66) with 40 lesions provided by 20 patients. Furthermore, assuming a 6-month incidence rate of 0.50, the bounds on the 95% exact CI will not extend beyond these limits: (0.38, 0.62) with 70 lesions provided by 35 patients.

Following the description of the two-stage design below is a sample size justification based on the precision associated with 95% CIs utilizing assumptions made with patient-level data.

## 6.2 Futility Monitoring

Futility monitoring will be conducted to stop the trial early if there is no observed benefit at the patient-level. The patient-level LC rate at 6-months will be used to monitor the trial for futility. We will estimate the LC rate at 6 months. The Green-Dahlberg two-stage design (<http://www.swogstat.org/stat/public/Help/twostage.html>) will be used to terminate the trial early for futility. The null hypothesis is that the 6-month LC rate is  $\leq 55\%$  and is not as effective as previously believed, thus requiring early termination of the trial for futility. The alternative hypothesis is that the LC rate at 6-months is clinically advantageous as demonstrated by a 6-month LC rate  $\geq 75\%$ . Hypothesis testing will be conducted using a one-sided test,  $\alpha = 0.05$ , and Type II error of 0.20. The probability of stopping at the end of Stage 1 is 0.409 if the null hypothesis is true, and the probability of stopping at the end of Stage 1 is 0.014 if the alternative hypothesis is true.

We will enroll a total of 35 evaluable patients. Initially, 20 patients will be enrolled in the first Stage of the study and evaluated for response at 6-months from day 1 of radiation treatment. If there are at least 11 patients among the first 20 who achieve LC at 6-months, then an additional 15 patients will be enrolled and evaluated. Note that the 20th patient in the first Stage must be evaluated for response prior to continuing to the second stage when less than 11 patients have experienced LC at 6-months. Finally, if there are at least 25 patients achieving LC at 6-months among all 35 patients, then we will reject H0. The statistical assessments will be used to design and appropriately power a Phase III study if warranted based on the outcomes we observe in this Phase II study.

Figure 1 Study Schema

[figure not shown]

Table 1. Description of the 2 Stage Design

|                                                                                 |                            |  |
|---------------------------------------------------------------------------------|----------------------------|--|
|                                                                                 | Study Cohort               |  |
| Null Hypothesis                                                                 | LC at 6 months $\leq 55\%$ |  |
| Alternative Hypothesis                                                          | LC at 6 months $\geq 75\%$ |  |
| Sample Size for Stage 1 (n1)                                                    | 20                         |  |
| Sample Size for Stage 2 (n2)                                                    | 15                         |  |
| Total Sample Size (n)                                                           | 35                         |  |
| Terminate Cohort for Futility if this many Success (A1) are observed in Stage 1 | 10 or fewer out of 20      |  |
| Continue to Stage 2 if this many Successes are observed                         | 11 or more out of 20       |  |
| # of LCs (R2) required to reject H0 at the end of the trial                     | 25 or more out of 35       |  |

For patient-level data, we will report the estimated LC rate at 6-months along with a 95% exact CI for the study cohort. Assuming a LC rate of 0.50, the bounds of the 95% exact CI will not extend beyond these limits: (0.27, 0.73) with 20 patients. Assuming a LC rate of 0.60, the bounds on the 95% exact CI will not extend beyond these limits: (0.42, 0.76) with 35 patients.

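### Section 6.2 states a Type II error of 0.20 for the patient-level two-stage test, but the rule as written has a Type II error of 0.24 (power 0.758) at a 75% local control rate

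*Protocol*

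**What the plan says.** Section 6.2 uses a Green-Dahlberg two-stage design on the patient-level 6-month LC rate, with a null of at most 55% and an alternative of at least 75%. On the error rates it says "Hypothesis testing will be conducted using a one-sided test", with alpha 0.05 "and Type II error of 0.20". It gives the probability of stopping after stage 1 as 0.409 under the null and 0.014 under the alternative.

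The decision rule appears twice. The text of Section 6.2 says that after stage 2, "if there are at least 25 patients achieving LC at 6-months among all 35 patients, then we will reject H0". Table 1 in the same section repeats the cutoff as "25 or more out of 35" and gives the stage 1 rule: stop at 10 or fewer of 20, continue at 11 or more. Neither place gives the attained alpha or power of the complete rule.

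For estimation, the text below Table 1 says "we will report the estimated LC rate at 6-months along with a 95% exact CI for the study cohort". Section 6.3 makes this interval two-sided.

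**The concern.** The stage sizes, the stage 1 bound and the final cutoff together fix the error rates, so the stated Type II error can be checked exactly. The stopping probabilities are quoted to three decimals for this specific rule. A reader will therefore take the Type II error beside them as a property of the same rule, and conclude that a true LC rate of 75% would be detected with 80% probability. If that is wrong, the test's chance of missing the LC rate the protocol calls clinically advantageous is understated. This is the only formal efficacy test in the document with a stated error rate.

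**Working it through.** **Inputs, all from Section 6.2 and its Table 1.** Null rate 0.55; alternative rate 0.75; one-sided test; stage 1 n = 20, stop at 10 or fewer; stage 2 n = 15; reject at 25 or more of 35. Nothing is assumed beyond independent patients with a common LC rate p.

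**Step 1: reproduce the plan's own stopping probabilities.** P(stop at stage 1) = P(Bin(20, p) ≤ 10).

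- p = 0.55: 0.4086 (stated 0.409)
- p = 0.75: 0.0139 (stated 0.014)

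Both agree, so the stage 1 rule has been read as intended.

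**Step 2: the complete rule.** P(reject) = Σ over x = 11 to 20 of P(Bin(20, p) = x) × P(Bin(15, p) ≥ 25 − x).

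- p = 0.75: power 0.7579, so Type II error = 1 − 0.7579 = 0.2421 (stated 0.20)
- p = 0.55: attained one-sided alpha 0.0354 (limit 0.05)

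Power is 0.80 − 0.758 = 0.042 below the stated value. By the same formula it is 0.800 at p = 0.76 and 0.838 at p = 0.77.

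**Step 3: is the futility look the cause?** No. A single-stage test rejecting at 25 or more of 35 has power 0.7581 and alpha 0.0354, practically the same.

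**Step 4: would another final cutoff give the stated pair?** Holding 20 + 15 and the stage 1 bound of 10:

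| Reject at | Alpha (p = 0.55) | Power (p = 0.75) |
|---|---|---|
| 23 of 35 | 0.132 | 0.922 |
| 24 of 35 | 0.073 | 0.857 |
| **25 of 35** | **0.035** | **0.758** |
| 26 of 35 | 0.015 | 0.626 |

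No row has alpha of at most 0.05 together with power of at least 0.80. The protocol's cutoff is the most powerful one that holds alpha.

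**Step 5: a possible source of 0.20.** A one-sample normal approximation with one-sided alpha 0.05 and power 0.80 gives n = {[1.645·√(0.55·0.45) + 0.842·√(0.75·0.25)] / 0.20}² = 34.97, that is 35 patients. This ignores the integer cutoff that the trial will apply. The protocol does not say how its figure was obtained, so this is only a plausible origin.

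**Step 6: the interval at the cutoff.** Clopper-Pearson limits:

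- 25/35: two-sided 95% 0.537 to 0.854; one-sided 95% lower bound 0.564
- 26/35: two-sided 95% lower limit 0.567

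The two-sided 95% interval includes 0.55 at exactly 25 of 35 although the test rejects there. At 26 or more it excludes 0.55. The probability of finishing with exactly 25 of 35 is 0.13 at p = 0.75 and 0.02 at p = 0.55.

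**The case against.** The best defence is that alpha 0.05 and Type II error 0.20 are nominal targets and that discreteness always moves the attained values. For alpha this succeeds. In an exact discrete test 0.05 is a ceiling, and 0.035 lies below it. A reader might count 0.035 against 0.05 as a second error, but it is only an attained value worth reporting. For the Type II error the defence fails: 0.242 is above the target, does not round to 0.20, and no attained figure is given elsewhere.

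A reader might also infer that the planned 95% interval contradicts the test. The documents do not support that. The decision is made on a count, nothing makes the interval decide it, and a two-sided 95% interval leaves 2.5% in each tail while the test uses 5% in one. The two part company among rejecting outcomes only at exactly 25 of 35. This is a presentational matter.

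A third stronger reading is that these error rates are the only justification for the trial's size and its go/no-go decision. They are not. Section 6.0 makes lesion failure the primary endpoint, Section 6.1 sizes it by the precision of exact intervals, and the text below Table 1 gives patient-level precision as well. The stage 1 decision is described correctly.

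Finally, the shortfall is small. Keeping the stage 1 rule, 20 + 17 patients with rejection at 26 or more of 37 gives alpha 0.0426 and power 0.8055, two patients more than planned. Section 6.2 also bases a possible Phase III on the outcomes observed, not on this trial's nominal power. These facts limit the severity; they do not make the stated figure right.

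**Conclusion.** One stated figure is wrong. For the rule as written, the Type II error at a 75% LC rate is 0.242, not 0.20: about 24 of 100 such trials would fail to reject, against the 20 of 100 stated. The result rests only on the protocol's own design parameters and the exact binomial distribution. The agreement of the stopping probabilities shows that the stage 1 rule was read correctly, and the final cutoff is stated identically in the text and in Table 1. Attained alpha is within its limit, the interim rule is sound, and the cutoff is the best available for these stage sizes and this stage 1 bound. Severity is moderate: the error concerns the patient-level test, while the primary endpoint is lesion-level failure sized by confidence interval precision.

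**What to change.** Keep the sample size, stage sizes and cutoffs. In Section 6.2 and Table 1, replace the Type II error of 0.20 with the attained properties of the rule: one-sided alpha 0.035 and power 0.76 (Type II error 0.24) at an LC rate of 75%, with 80% power reached at an LC rate of about 76%.

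Optionally, report the one-sided 95% lower bound (0.564 at 25 of 35) beside the planned two-sided 95% interval, with a sentence saying that the bound corresponds to the one-sided test. This prevents confusion if the result is exactly 25 of 35.

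The cost is a wording change and a slightly less favourable stated power; no patients are added and no decision changes. If the sponsor does require both nominal targets, a redesign is needed: with the same stage 1, 20 + 17 patients and rejection at 26 or more of 37 meets them, at the cost of two more evaluable patients.

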### 6.3 Analysis of Study Results

Descriptive statistics will be used to explore the data for quality issues, identifying outliers, and providing summaries of data distributions. T-tests or Wilcoxon rank sum tests will be used to compare continuous variables between patient groups of interest. Categorical data will be summarized using frequencies and percentages. Chi-square or Fisher's exact tests will be used to compare categorical variables between patient subgroups of interest. The LC estimates at the patient-level and incidence of failure at the lesion-level will be reported and will be accompanied by a 2-sided exact 95% confidence interval.

Rates of local control will be estimated at each of the follow-up assessments. Intracranial progression-free survival and overall survival will be summarized using the Kaplan-Meier method. Intracranial progression-free survival will be defined as the time from enrollment to either the first observation of progressive disease in the brain or death due to any cause. For intracranial PFS, patients not experiencing a death or intracranial progression will be censored at the last tumor assessment, approximately 1 year from day 1 of the start of radiation treatment. Intracranial PFS and OS will be summarized using the Kaplan-Meier method, and the 50th percentile of the K-M distribution will determine the median intracranial PFS or OS.

Finally, the cost data will be summarized using descriptive statistics such as the mean, median, standard deviation, and range. Comparisons in cost between treatment modalities will be evaluated using a paired t-test where each patient will serve as his or her own control to determine if the cost of FFSRT is comparable to standard treatment.

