### **Secondary Objectives**

1. To assess 6-month local control, intracranial progression-free survival and overall survival.
2. To collect data on charges and reimbursements of patients treated with FFSRT to compare those charges and reimbursements if the same patients had been treated with single-fraction, frame-based Gamma Knife SRS.

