### **Ineligibility**

Patients and/or their disease meeting any of the following criteria are ineligible for enrollment.

1. Less than 18 years old.
2. Five or more metastatic brain lesions.
3. Brain lesion(s) greater than 5 cm in diameter.
4. Lesion(s) involving the brainstem, optic chiasm or optic nerve(s).
5. Patients unable to have IV contrast for CT and MRI imaging.
6. Patient unable to have an MRI of the brain.
7. Patients willing to be treated with frame-based Gamma Knife SRS at MD Anderson main campus or MD Anderson at The Woodlands.
8. Positive pregnant status confirmed by serum or urine pregnancy test.
9. Primary small cell lung cancer, myeloma, lymphoma, leukemia, or other histologies not optimally treated with SRS.
10. Patients currently receiving chemotherapy/biologic/immunotherapy as these need to be held during FFSRT
11. Prior whole brain radiotherapy or conventional external beam radiotherapy.

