## **6.0 Statistical Considerations**

Patients will be treated based on an optimal plan derived for each patient. We plan to enroll a maximum of 35 patients. We expect to encounter 2 lesions requiring treatment per patient. The primary endpoint is lesion failure within the first 6 months based on imaging assessments for each lesion. The evaluable study population will consist of patients who reach the 6-month evaluation point for local control. We will assume that failure of a lesion is independent of failure for all other lesions. However, an exploratory analysis will be conducted to assess this assumption as evidence suggesting within patient correlation is not available in the published literature.

Patients' lesions will be followed for failure starting on day 1 of radiation treatment in 3-month intervals (+/-2 months) for up to 1-year. Patients unable to complete at least 80% of their prescribed dose will be replaced.

We plan to evaluate efficacy at the level of the lesion. However, this study will monitor futility attributable to patient benefit at the patient-level using local control in consort with the assessment criteria for lesions.

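### Section 6.3 uses a paired t-test of zero difference, against an SRS amount no patient incurred, to settle whether FFSRT cost is comparable; that test cannot answer the question in either direction

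*Protocol*

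**What the plan says.** The second item under Secondary Objectives (Protocol section 1.0) is to gather charges and reimbursements for FFSRT and "to compare those charges and reimbursements if the same patients had been treated with single-fraction, frame-based Gamma Knife SRS". The SRS side is therefore openly hypothetical.

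Section 6.3 turns this into two analyses. First, "the cost data will be summarized using descriptive statistics such as the mean, median, standard deviation, and range". Second, "Comparisons in cost between treatment modalities will be evaluated using a paired t-test", in which "each patient will serve as his or her own control to determine if the cost of FFSRT is comparable to standard treatment".

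The Ineligibility list excludes "Patients willing to be treated with frame-based Gamma Knife SRS at MD Anderson main campus or MD Anderson at The Woodlands", and section 7.0 offers enrolment to those unable or unwilling to be treated at those sites. The cohort therefore contains no observed SRS charge for the lesions under study.

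On size, section 6.0 states "We plan to enroll a maximum of 35 patients". Section 6.2 allows the trial to stop after the 20 patients of stage 1. The sample-size arguments in sections 6.1 and 6.2 concern lesion failure and local control; none concerns cost. Section 6.3 gives no alpha or sidedness for the cost test and plans no confidence interval for the cost difference.

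**The concern.** The test and its stated purpose do not match. A paired t-test takes zero mean difference as its null hypothesis. It can give evidence that costs differ; it has no outcome that gives evidence that they are alike. Of its two possible results, only non-significance could be taken to support comparability, and non-significance also arises from small numbers or wide spread. A significant result does not settle the matter either, because with little spread a difference too small to matter will be significant.

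The pairing adds a second problem. Calling the patient their own control suggests two measurements on one person. Here one member of the pair is measured and the other is assigned. The standard error of the test reflects only how the differences vary between patients. An error in the assigned SRS amount that is common to all patients shifts every pair the same way and does not appear in that standard error.

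At stake is a secondary conclusion: a published statement that FFSRT costs are, or are not, comparable to SRS, resting on a p-value that cannot carry it.

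**Working it through.** The protocol states no cost figure, SD, margin or power, so there is nothing of its own to reproduce. The check asks how the named test behaves.

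**Inputs**
- n = 35 (maximum, section 6.0); n = 20 if stopped after stage 1 (section 6.2).
- Two-sided alpha 0.05: an assumption. The one-sided 0.05 in section 6.2 belongs to the local-control hypothesis.
- True mean difference and SD of the paired differences, both as a percentage of mean cost: assumptions, shown over a range because the protocol gives none.

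**Formula.** Let d = true mean difference / SD of paired differences. The t statistic follows a noncentral t distribution with n − 1 degrees of freedom and noncentrality d√n. The chance of non-significance is P(|T| < t_crit), with t_crit = 2.032 for n = 35 and 2.093 for n = 20.

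**A real difference that the test misses**

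| True difference | SD | d | d√35 | Non-significant, n = 35 | Non-significant, n = 20 |
|---|---|---|---|---|---|
| 20% | 80% | 0.25 | 1.48 | 70% | 81% |
| 15% | 50% | 0.30 | 1.77 | 59% | 75% |
| 20% | 50% | 0.40 | 2.37 | 37% | 60% |
| 20% | 25% | 0.80 | 4.73 | 0.4% | 8% |

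**A trivial difference that the test flags.** True difference 3%, SD 5%: d = 3/5 = 0.6 and d√35 = 3.55. The result is significant in 93% of trials at n = 35.

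The verdict of the test thus follows the spread and the number of patients, not whether the costs are close enough to matter.

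**What estimation would give.** The 95% CI half-width for the mean difference is t_crit/√n SDs: 2.032/√35 = 0.34 SD, and 2.093/√20 = 0.47 SD. If the SD were 50% of mean cost, that is about ±17% (0.34 × 50%) at n = 35 and ±23% (0.47 × 50%) at n = 20.

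**Whether a margin rule would work instead.** The table gives the chance, by simulation with a true difference of zero, that the CI falls wholly inside ± the margin at n = 35:

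| Margin (SDs of paired difference) | 95% CI inside | 90% CI inside (two one-sided 5% tests) |
|---|---|---|
| 0.3 | 1.6% | 11% |
| 0.4 | 27% | 50% |
| 0.5 | 64% | 79% |

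A formal equivalence claim is therefore feasible only for a fairly wide margin.

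**The case against.** **No decision rule is stated.** A reader might infer that the plan will treat p > 0.05 as equivalence. The protocol nowhere says so, and it also plans the mean, median, SD and range, so the size of any difference could be seen beside the p-value. This stands: equivalence by non-significance cannot be attributed to the plan as a rule. What remains is that the test is given the task of determining comparability and has no other result that could serve it.

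**The direction of error is unknown.** A reader might infer that the plan is tilted towards finding costs comparable. That requires a large paired SD and, in the usual argument, skewed charges; the protocol documents neither. If amounts follow tariffs, the SD may be small and the opposite error would dominate. This also stands, and is why both errors are shown above. The supplementary table reports 73 patients, not 35. It may describe results rather than the plan, but at n = 73 the 59% falls to 28% and the 37% to 8%. The mismatch between test and aim is the same at any n.

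**Unseen detail.** How the SRS amount is derived may be in an SAP that is not shown, and a fixed tariff would have no sampling error to ignore. That is fair, and the missing derivation is not part of this point. But with a fixed tariff the pairing reduces to a one-sample test against a constant, so describing each patient as their own control still overstates what is observed.

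**Wording of cost.** One might read section 6.3 as dropping one of the two quantities in the objective. The plural reference to comparisons can reasonably cover both charges and reimbursements, so no contradiction is claimed.

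**The rationale.** The cost-containment argument in section 2.0 rests on FFSRT being as effective and sparing centres extra equipment, not on a comparison of charges. The cost test should not be presented as deciding that argument.

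**Conclusion.** The point holds as a mismatch between a named test and its stated aim, made worse by a comparator that is assigned and not observed. Adding detail in an SAP would not cure it, because the sentence in section 6.3 names the wrong tool for the question.

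Its size cannot be fixed from the protocol. Over the assumed SDs at n = 35, a true 20% difference goes undetected in anything from 0.4% to 70% of trials, and a 3% difference can be significant in 93%. These figures assume approximately normal paired differences, two-sided 0.05 and the SDs shown.

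This concerns a secondary objective. The primary endpoint, the futility rule and the safety monitoring are not affected.

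**What to change.** In section 6.3, replace the t-test sentence with estimation. Report the mean paired difference (FFSRT minus assigned SRS amount) with a 95% CI, once for charges and once for reimbursements, and label it a modelled comparison with the SRS amount the same patients would have been assigned. Delete the clause about determining comparability.

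If the sponsor wants to keep the word comparable, it should be tied to a margin fixed before the cost data are seen, with a note that 35 patients have little chance of meeting a margin much below 0.5 SD of the paired difference. For that reason a margin rule is an option and not the default.

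The cost is a change of wording; no extra patients or data are needed. The downside is that the trial can no longer declare costs comparable on the strength of a p-value, and the intervals may be wide.
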